**Fig 3 pone.0295293.g003:**
[figure not shown]
Plot of mean simulated power with 95 percentile (2.5 & 97.5%) for select DNAm differences.

Data quality and integrity will be ensured before the conduct of statistical analysis. Prior power analyses for each planned analysis were conducted to ensure that each analysis was appropriately powered. All post-hoc tests will be controlled for multiple comparisons (i.e., Type I error). ANCOVA will also be used because it is better at controlling for chance imbalances in randomized groups at baseline, avoids regression to the mean issues, and is generally more statistically powerful in detecting differences [114].

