**Fig 1 pone.0295293.g001:**
[figure not shown]
Study period. Schedule of enrollment, interventions, and assessments.

**Table 1 pone.0295293.t001:** Sample size estimation based on preliminary date. *Assumes n = 125 per group complete cases and *α* = 0.05; r-squared of 5 covariates is 0.30, **The smallest mean difference necessary to ensure > 80% power, assuming pooled SD observed in the pilot.

Outcome evaluated at 6 months	RiSE Mean	Control Mean	|Δ| Means	Pooled SD	Effect size	Power*	Mean difference for 80% power**
	Observed: Pilot Data @ 8 weeks						
WCQ-Active coping	23.76	24.77	1.01	8.24	0.06	21%	2.45
WCQ-Avoidance coping	8.14	14.38	6.24	5.25	0.59	>99%	1.56
WCQ-minimize situation	11.21	14.04	2.83	4.36	0.32	>99%	1.30
DASS-21: Depression	1.45	3.13	1.68	3.09	0.27	>99%	0.92
DASS-21: Anxiety	2.39	3.31	0.92	3.41	0.13	72%	1.02
DASS-21: Stress	4.45	5.90	1.45	4.05	0.18	92%	1.20
TNF-a	0.95	1.00	0.05	0.36	0.07	26%	0.11
High-sensitivity C-reactive protein (hsCRP)	3.83	7.24	3.41	6.30	0.27	>99%	1.88

*Resilience*, *Stress*, *and Ethnicity* (RiSE) [37–39], is a group-based, 8-week intervention that integrates cognitive-behavioral strategies [40] focused on the biopsychosocial impact of racism [41, 42], racial identity development [43–45], and empowerment [46]. The conceptual model for the study is based on allostatic load theory [47] which posits that accumulating stress or “wear and tear” results in negative physiological consequences. **See Fig 2.**

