### Procedures

Detailed descriptions of this study have been previously discussed [90]. Briefly, this convenience sample will include 300 self-identified AA women residing in either the Chicagoland (n = 150) or New York City (n = 150) area between the ages of 50 and 75 years with risk factors for CMD [91]. Participants will be randomized to either an 8-week RiSE intervention or a Health Education Program (HEP) (attention control). Potential participants will be pre-screened for eligibility over the phone and will be followed by an appointment for further screening if the potential participant is eligible. After collecting informed consent for obtaining inflammatory markers and DNAm samples, the samples will be stored in a lab for processing and frozen for later batch analysis. DNAm samples will be stored at 4°C. Specimens will be shipped overnight on dry ice to respective labs for analysis per best practice guidelines [92]. Individuals will contribute data for up to four-time points (baseline, 4 weeks (mid-intervention), 8 weeks (completion of intervention), and 6 months post-intervention). Data will be collected from participants using an Audio Computer-Assisted Self-Interview system (ACASI) [93]. Perceived stress, depression, fatigue, and sleep disturbance symptoms will be analyzed via the Perceived Stress Scale (PSS-10) [94], Patient Health Questionnaire 9 (PHQ 9) [95], NIH PROMIS Fatigue Short Form 8a [96], and NIH PROMIS Short Form v1.0 [97].

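### The article says every planned analysis is appropriately powered, but its Table 1 shows 21% for active coping and 26% for TNF-a, and powers symptoms on an instrument that Procedures does not list

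*Protocol article*

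**What the plan says.** The paragraph after Fig 3, at the end of the Power analysis section, says: "Prior power analyses for each planned analysis were conducted to ensure that each analysis was appropriately powered". It names no exception.

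Table 1 lists eight outcomes under the column heading "Outcome evaluated at 6 months", with differences taken from a pilot at 8 weeks. Its footnotes assume "n = 125 per group complete cases and *α* = 0.05; r-squared of 5 covariates is 0.30" and define the last column as "The smallest mean difference necessary to ensure > 80% power, assuming pooled SD observed in the pilot". Two rows read "WCQ-Active coping 23.76 24.77 1.01 8.24 0.06 21% 2.45" and "DASS-21: Anxiety 2.39 3.31 0.92 3.41 0.13 72% 1.02"; in each, the last two entries are the power and the difference needed for 80% power. The TNF-a row gives means of 0.95 and 1.00, SD 0.36, power 26% and 0.11 for 80% power. The three symptom rows are all DASS-21 subscales (depression, anxiety, stress).

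Procedures names the symptom instruments: "Perceived stress, depression, fatigue, and sleep disturbance symptoms will be analyzed via the Perceived Stress Scale (PSS-10"), followed by PHQ-9, a PROMIS fatigue form and a further PROMIS short form. DASS-21 appears nowhere outside Table 1. The Abstract lists perceived stress, depressive symptoms, fatigue, sleep, inflammatory burden and coping as the measures.

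**The concern.** A blanket assurance of adequate power stands beside a table in which two outcomes from the trial's stated domains, coping and inflammation, have about one chance in four or less of reaching significance at the pilot differences. If the assurance is carried into the results, a null finding on TNF-a or active coping could be taken as a well-powered negative.

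The second part concerns coverage. The power shown for stress and depression belongs to DASS-21, with its own pilot means and SDs. It does not carry over to PSS-10 or PHQ-9, and the two PROMIS domains, fatigue and sleep, have no row under any instrument.

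**Working it through.** **Inputs (Table 1 and its footnotes).** n = 125 complete cases per group, alpha 0.05, R² = 0.30 with 5 covariates, and the pilot difference and pooled SD of each row. The article does not state sidedness; two-sided is assumed because it reproduces the table.

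**Formulas.**
- Adjusted SD = SD × √(1 − 0.30) = 0.8367 × SD.
- Standard error of the difference = adjusted SD × √(2/125) = adjusted SD × 0.1265.
- Power ≈ Φ(difference/SE − 1.960).
- Difference for 80% power ≈ (1.960 + 0.842) × SE.

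**Reproducing Table 1.**

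| Row | SE | Difference/SE | Power, recomputed | Power, stated | 80% difference, recomputed | 80% difference, stated |
|---|---|---|---|---|---|---|
| Active coping | 8.24 × 0.8367 × 0.1265 = 0.872 | 1.01/0.872 = 1.158 | 21.1% | 21% | 2.44 | 2.45 |
| TNF-a | 0.36 × 0.8367 × 0.1265 = 0.0381 | 0.05/0.0381 = 1.312 | 25.9% | 26% | 0.107 | 0.11 |
| DASS-21 anxiety | 3.41 × 0.8367 × 0.1265 = 0.361 | 0.92/0.361 = 2.549 | 72.2% | 72% | 1.01 | 1.02 |
| DASS-21 stress | 4.05 × 0.8367 × 0.1265 = 0.429 | 1.45/0.429 = 3.383 | 92.3% | 92% | 1.20 | 1.20 |

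The other four rows exceed 99%, as stated. A noncentral t calculation on 243 degrees of freedom agrees within half a point. Leaving out the covariate adjustment gives 16%, 19% and 57% for the first three rows, and a one-sided 0.05 test gives 31%, 37% and 82%. Neither matches the table, so the low figures are genuine results of the plan's own assumptions and not misprints.

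**Rounding.** The TNF-a inputs are coarse. Letting the difference run from 0.045 to 0.055 and the SD from 0.355 to 0.365 moves power only between 21% and 31%.

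**How far short.**
- The difference needed for 80% power is 2.45/1.01 = 2.4 times the pilot difference for active coping and 0.11/0.05 = 2.2 times for TNF-a. For anxiety it is 1.02/0.92 = 1.1 times.
- Completers per group for 80% power at the pilot difference, 2 × (2.802)² × adjusted SD² / difference², come to 732 for active coping, 570 for TNF-a and 151 for anxiety, against 125 planned.
- If all 300 enrolled women completed (150 per group), power would be 24.5%, 30.1% and 79.7%.

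**Direction.** The active-coping means are 23.76 (RiSE) and 24.77 (control), so RiSE − control = −1.01.

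**Instruments.** Power for PSS-10, PHQ-9 and the PROMIS forms cannot be computed at an expected effect, because the article gives no SD or difference for them. A standardised detectable difference can be given:
- R² = 0.30: 2.802 × 0.1265 × 0.8367 = 0.297 SD (0.298 by the noncentral F), about 0.30 SD.
- R² = 0: 2.802 × 0.1265 = 0.354 SD by the normal formula; rescaling the noncentral figure, 0.298/0.8367 = 0.356 SD, about 0.36 SD.

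**The case against.** The best defence is that 21% and 26% are power at differences seen in a pilot at 8 weeks, not at a declared target, and that Table 1's last column shows what each analysis can detect with 80% power. It stands that the authors examined detectability for these rows and calculated it correctly. It does not rescue the sentence. The article never calls those differences targets or clinically relevant, they are more than twice the pilot differences for these two outcomes, and any trial has 80% power for some difference.

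For active coping it is also fair to say that 21% is two-sided power at an adverse pilot difference, and so says little about power for the hoped-for improvement. TNF-a is therefore the cleanest example: a planned marker, lower with RiSE in the pilot, with low power.

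A reader might infer more than the article supports:
- **Three of eight planned outcomes are underpowered.** Anxiety is in Table 1 but not among the symptoms in the Abstract or Procedures. The 72% counts only if anxiety is analysed.
- **The absolute-difference column conceals the direction.** Both arm means are printed and labelled in the same row, so the sign is open to any reader.
- **IL-6, IL-1β and IFN-γ were never powered.** They have no row, but the article condenses a fuller description and says the analyses were done, not that all are shown.
- **The trial has 80% power for 0.30 SD on every continuous outcome.** That needs R² = 0.30, which is given only for Table 1.

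It is also true that TNF-a's 26% is printed openly, which limits the risk of misreading.

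**Conclusion.** The point holds as an inconsistency between the article's text and its own table; it is not an arithmetic error. The claim that each planned analysis is appropriately powered is contradicted for active coping (21%) and TNF-a (26%) at the pilot differences, judged against the 80% benchmark that Table 1 itself uses. This rests on 125 completers per group, two-sided alpha 0.05, R² = 0.30 and the pilot SDs.

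Separately, the symptom power shown is for DASS-21 and not for the four instruments in Procedures. The article should be consistent on this whatever a fuller document contains.

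Nothing here touches the methylation power simulation, and no change to sample size or tests follows.

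**What to change.** 1. Limit the sentence to the analyses that reach 80% power.
2. State that active coping and TNF-a, and anxiety if it is analysed, are below 80% at the pilot differences, and that null results on them will be reported as estimates with confidence intervals and not as evidence of no effect.
3. Reconcile DASS-21 in Table 1 with the PSS-10, PHQ-9 and PROMIS forms in Procedures.
4. For the instruments that will be analysed, give the standardised difference detectable with 80% power at 125 per group together with its R² assumption: about 0.30 SD if R² = 0.30 and about 0.36 SD if R² = 0. Say that both are before any design effect, since RiSE is delivered in groups.

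The cost is wording, and a power statement that reads less favourably.

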#### Genomic data analysis

Using the pre-processed and quality-controlled methylation data expressed as beta values which are the percentage methylation at each CpG site at specific targeted candidate genes, we will determine changes in methylation (Δ***β***) at every site as the difference between methylation at baseline and methylation at post-intervention. Negative Δ***β*** indicates a decrease in methylation from baseline to post-intervention, and a positive value indicates an increase in methylation from baseline to post-intervention. Association analyses will be performed to detect differentially methylated sites on the targeted candidate genes between the intervention and non-intervention groups using the Δ***β*** with adjustment for age, health behaviors, early life adversity, hybridization batch, and top principal components of the probes as covariates. To adjust for multiple testing, we will use False Discovery Rate (FDR) adjustment with an FDR of <0.05 regarded as statistically significant. All analyses will be performed in R software using the Bioconductor R package ‘limma’ [115]. To assess the relationship between inflammatory burden (IL-6, TNF-α, IL-1β, IFN-γ, CRP) and Δ***β*** among the study samples, we will repeat the above association analyses with the inclusion of individual inflammatory protein measure.

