## Abstract

RiSE study aims to evaluate a race-based stress-reduction intervention as an effective strategy to improve coping and decrease stress-related symptoms, inflammatory burden, and modify DNA methylation of stress response-related genes in older AA women. This article will describe genomic analytic methods to be utilized in this longitudinal, randomized clinical trial of older adult AA women in Chicago and NYC that examines the effect of the RiSE intervention on DNAm pre- and post-intervention, and its overall influence on inflammatory burden. Salivary DNAm will be measured at baseline and 6 months following the intervention, using the Oragene-DNA kit. Measures of perceived stress, depressive symptoms, fatigue, sleep, inflammatory burden, and coping strategies will be assessed at 4 time points including at baseline, 4 weeks, 8 weeks, and 6 months. Genomic data analysis will include the use of pre-processed and quality-controlled methylation data expressed as beta (***β***) values. Association analyses will be performed to detect differentially methylated sites on the targeted candidate genes between the intervention and non-intervention groups using the Δ***β*** (changes in methylation) with adjustment for age, health behaviors, early life adversity, hybridization batch, and top principal components of the probes as covariates. To account for multiple testing, we will use FDR adjustment with a corrected p-value of <0.05 regarded as statistically significant. To assess the relationship between inflammatory burden and Δ***β*** among the study samples, we will repeat association analyses with the inclusion of individual inflammation protein measures. ANCOVA will be used because it is more statistically powerful to detect differences.

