### Data analytic plan

#### Power analysis

We will focus primarily on the tested CpG sites that are true positives, i.e., detected CpG sites with meaningful differential DNAm. There is currently no standard threshold for meaningful differential DNAm, though previous studies have used thresholds of 5–20% [112] for meaningful differential DNAm, and for this study, we use a conservative threshold of 10%. Using the R package ‘pwrEWAS’ [113], we performed simulations to evaluate sample sizes required to detect effect sizes (percent differences) of 7.5%, 10%, 12.5%, and 15% in CpG-specific methylation across 4000 CpGs on our 20 candidate genes with at least 80% power. We need 200 total subjects (150 per group) to detect a difference of at least 10% with at least 80% power across a set of CpG sites (**Fig 3**). Our simulations also indicated that the power to detect at least one differentially methylated CpG out of the set of 4000 is above 85%.

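### The methylation model analyses Δβ without the same-CpG baseline β as a covariate: a valid analysis, but less efficient than the ANCOVA the article itself favours

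*Protocol article*

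**What the plan says.** The Genomic data analysis section defines the outcome at each CpG "as the difference between methylation at baseline and methylation at post-intervention", signed so that a negative value is a fall. The arms are then compared on Δβ in limma "with adjustment for age, health behaviors, early life adversity, hybridization batch, and top principal components of the probes as covariates", and the Abstract gives the same list. Significance is "an FDR of <0.05 regarded as statistically significant". The analyses involving inflammatory proteins reuse this model with a protein measure added.

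The paragraph just before that section, at the end of Power analysis, says "ANCOVA will also be used because it is better at controlling for chance imbalances in randomized groups at baseline", and goes on to cite regression to the mean and power. The Abstract closes with "ANCOVA will be used because it is more statistically powerful to detect differences". Neither sentence names the outcomes to which ANCOVA applies.

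**The concern.** A comparison of Δβ without baseline β is a change-score analysis. It fixes the slope of 6-month β on baseline β at 1, where ANCOVA estimates it. The three advantages the article credits to ANCOVA (power, handling of chance imbalance, protection from regression to the mean) are advantages over this kind of analysis. As written, the central genomic model does without them, even though saliva methylation is measured at baseline in every participant.

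Two things are at stake. One is power, which is lost wherever β is not highly stable over 6 months. The other is interpretation: at a CpG where the arms differed by chance at baseline, a change in Δβ cannot be told apart from regression to the mean.

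**Working it through.** **Inputs.** 125 complete cases per arm (Table 1 caption; 250 in total under Potential pitfalls). About 4000 CpGs on 20 genes (Power analysis). FDR below 0.05 (Genomic data analysis). The correlation rho between baseline and 6-month β is not given, so I assume a range of 0.2 to 0.95. The only related text, in the Introduction, reports wide inter-individual differences in methylation over time.

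**The article's own figures.** Table 1 covers the non-genomic outcomes and reproduces as covariate-adjusted power, using SD × √(1 − 0.30), 125 per arm and two-sided alpha 0.05. For DASS-21 stress, the adjusted SD is 4.05 × √0.70 = 3.39, the standard error is 3.39 × √(2/125) = 0.429, and 1.45/0.429 = 3.38, so power is 92.3% (stated 92%). Active coping, anxiety and TNF-α give 21.1%, 72.2% and 25.9% (stated 21%, 72% and 26%), and the other four exceed 99%. So adjusted power was planned for those outcomes, though the five covariates are not named. The methylation power comes from a pwrEWAS simulation whose inputs are not in the article, so it cannot be reproduced. (Its sample size, "We need 200 total subjects (150 per group) to detect a difference of at least 10" percent, does not add up, since 2 × 150 = 300. That is a separate matter.)

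**Efficiency.** With equal variance σ² at both visits, the per-participant variance behind the arm contrast is:

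- change score: 2σ²(1 − rho)
- ANCOVA: σ²(1 − rho²)
- ratio, ANCOVA to change score: (1 + rho)/2

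Set the effect so that ANCOVA has 80% power at 125 per arm. The change score's standardized effect is then smaller by a factor √((1+rho)/2). At rho = 0.5 and alpha 0.05: 2.802 × √0.75 = 2.426, and 2.426 − 1.960 = 0.466, giving 68%.

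| rho (assumed) | Variance ratio | Change-score power, alpha 0.05 | Change-score power, alpha 0.05/4000 | Per arm to match ANCOVA, 125 × 2/(1+rho) |
|---|---|---|---|---|
| 0.2 | 0.60 | 58% | 37% | 208 |
| 0.5 | 0.75 | 68% | 56% | 167 |
| 0.7 | 0.85 | 73% | 67% | 147 |
| 0.9 | 0.95 | 78% | 76% | 132 |
| 0.95 | 0.975 | 79% | 78% | 128 |

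The 0.05/4000 column is a Bonferroni-type bound, stricter than the planned FDR rule. Below rho = 0.5 the change score is less precise than ignoring baseline altogether, because 2(1 − rho) exceeds 1.

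**False positives.** A null simulation (20,000 replicates per rho, 125 per arm, tests at p < 0.05) gave:

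| rho | Overall, change score | Overall, ANCOVA | Given baseline p < 0.05, change score | Given baseline p < 0.05, ANCOVA | Share of change-score false positives at such CpGs |
|---|---|---|---|---|---|
| 0.2 | 5.1% | 5.0% | 29% | 5% | 28% |
| 0.5 | 5.1% | 4.9% | 19% | 4% | 19% |
| 0.7 | 5.2% | 5.3% | 14% | 6% | 13% |
| 0.9 | 5.1% | 5.0% | 8% | 4% | 7% |

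The overall error rate is nominal for both methods. About 5% of CpGs (0.05 × 4000 = 200) will be nominally imbalanced at baseline, and under the change score they take more than their share of the false positives.

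Analytically, a baseline imbalance of z moves the null change-score statistic by z × √((1 − rho)/2) in size. For z = 3.3 and rho = 0.3 this is 3.3 × 0.592 = 1.95 standard errors.

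**The case against.** Four points can be made for the plan as written.

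- **Error control.** A reader might infer that chance imbalance inflates false positives or the FDR. It does not. Randomization keeps the change-score contrast unbiased, and the simulated error rate is nominal. False positives move between CpGs but do not become more numerous. This stands in full.
- **The multiplicity threshold.** The shares of 7% to 28% refer to nominal p < 0.05, which the plan does not call significant. With few true effects, the first FDR rejection needs about p < 0.05/4000, or |z| = 4.37. In the example above the remaining SD is √0.65 = 0.81, so the chance of crossing is that of exceeding (4.37 − 1.95)/0.81 = 3.0, about 0.0014. Declared hits would therefore rarely arise this way. This also stands. The effect bears mainly on how nominal or ranked lists are read.
- **The ANCOVA sentence.** A reader might infer that the plan contradicts itself. The sentence names no outcome. It may refer only to the coping, symptom and inflammatory outcomes, and then nothing conflicts. It may also cover methylation, since it sits directly before the genomic section and closes the Abstract's genomic summary, and then the covariate list is incomplete. The text shows an ambiguity, not a proven contradiction. On either reading the listed model lacks baseline β.
- **Unknown rho.** The size of the loss rests on a figure outside the article. At rho 0.9 it is only about 2 points of power. Nothing here shows that the study misses its 80% target.

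The article is condensed, and a fuller plan may exist. But its stated purpose is to describe the genomic methods, and it gives the same covariate list twice, so the omission is a fair point to raise.

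**Conclusion.** The point holds as one of efficiency and interpretability. The stated Δβ model is valid, and FDR control is not weakened, because the p-values entering the adjustment are themselves valid. The documents do not support calling the analysis invalid or the study underpowered.

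For any rho below 1 the model is less efficient than the same model with baseline β added. Relative to 80% power under ANCOVA at 125 per arm and alpha 0.05, the loss is about 22 points at rho 0.2, 12 at 0.5, 7 at 0.7 and 2 at 0.9. These figures assume equal variances at the two visits and a common rho in both arms, with rho read as the correlation left after the listed covariates. Rho will differ between CpGs, so the gain is small at stable sites and material at noisy ones. This is an almost free improvement, not a mandatory correction.

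**What to change.** Regress 6-month β on arm, baseline β at the same CpG and the covariates already listed. Keeping Δβ as the outcome gives the same arm coefficient once baseline β is in the model. Carry the change into the Abstract and into the inflammatory-protein analyses that reuse the model. State that the ANCOVA sentence covers the methylation analysis, and name the other outcomes it covers.

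The covariate differs by CpG, and limma's standard fit uses one design matrix for all CpGs. There are two workable routes:

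- Fit CpG by CpG and apply limma's variance moderation (squeezeVar) afterwards.
- Fit both visits in limma with a common baseline mean for the arms and participant as a correlated (random) block. Entering participant as a fixed effect would bring back the change score.

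The cost is one degree of freedom, slightly more code than the single-design fit, and a sentence or two of text. No new data are needed. The choice should be fixed before the methylation data are analysed, so that it cannot depend on the results.
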